# A randomised feasibility trial of an intervention to support sharing of HIV status for 18–25-year olds living with perinatally acquired HIV compared with standard care: HIV Empowering Adults’ Decisions to Share—UK/Uganda Project (HEADS-UP)

**DOI:** 10.1186/s40814-020-00688-w

**Published:** 2020-09-24

**Keywords:** HIV, Disclosure, Perinatal, Feasibility, Intervention

## Abstract

**Abstract:**

**Background:**

Young adults with perinatally acquired HIV (PAH) face several challenges, including adhering to antiretroviral therapy (ART), managing the risk of onward HIV transmission and maintaining positive well-being. Sharing one’s HIV status with others (onward HIV disclosure) may assist with these challenges by facilitating emotional and practical support. Rates of HIV status sharing are, however, low in this population. There are no existing interventions focused on sharing one’s HIV status for young adults living with PAH. The HEADS-UP study is designed to develop and test the feasibility of an intervention to help the sharing of HIV status for young adults with PAH.

**Methods:**

The study is a 30-month multi-site randomised feasibility study across both a high-income/low-HIV prevalence country (UK) and a low-income/high-HIV prevalence country (Uganda). Phase 1 (12 months) will involve developing the intervention using qualitative interviews with 20 young people living with PAH (ten in the UK—18 to 29 years; ten in Uganda—18 to 25 years), 20 of their social network (friends, family, sexual partners as defined by the young person; ten in the UK, ten in Uganda) and ten professionals with experience working with young adults with PAH (five in the UK, five in Uganda). Phase 2 (18 months) involves conducting a randomised feasibility parallel group trial of the intervention alongside current standard of care condition in each country (main study) with 18- to 25-year olds with PAH. A sample size of 94 participants per condition (intervention or standard of care; 188 participants in total: 47 in each condition in each country) with data at both the baseline and 6-month follow-up time points, across UK and Ugandan sites will be recruited. Participants in the intervention condition will also complete measures immediately post-intervention. Face-to-face interviews will be conducted with ten participants in both countries immediately post-intervention and at 6-month follow-up (sub-study).

**Discussion:**

This study will be the first trial that we are aware of to address important gaps in understanding acceptable and feasible ways of delivering HIV status sharing support for young people living with PAH.

**Trial registration:**

ISRCTN Registry, ISRCTN31852047, Registered on 21 January, 2019. Study sponsor: Royal Holloway University of London. Sponsor contact: [contact]. Date and version: April 2020. Protocol version 3.5.

## Background

The World Health Organisation estimates that globally, around 5 million young people (15–25 years) are living with HIV, and a significant proportion of these have acquired HIV perinatally (perinatally acquired HIV (PAH)) [1]. In some low-income countries, young people are disproportionately affected by HIV. For example, in Uganda, youth (aged 10–24) comprise 33% of the population, but account for nearly 50% of the people living with HIV in the country [2]. About 78% of young people aged 15–24 living with HIV reside in sub-Saharan Africa [3].

The enhanced availability of antiretroviral therapy (ART), as well as the change in ART guidelines since 2015 [4], recommending ART for all people living with HIV irrespective of CD4 count or clinical stage, has led to a growing proportion of perinatally HIV-infected children surviving into adulthood [5]. The UK has a relatively small number of people living with PAH compared with other countries globally [5]. The majority of the UK cohort is of sub-Saharan African origin, with half born outside the UK [6]. Uganda has a much larger number of people living with PAH, although there are no precise estimates of the size of this population [7].

Although young people living with PAH share some similar challenges to those who are behaviourally infected (e.g., potentially compromised health and risk of onward transmission through sex) other stressors relate specifically to perinatal transmission. Longstanding HIV infection acquired prior to physiological and immunological development results in distinctive chronic clinical complications that can cause severe morbidity [8]. In addition to dealing with chronic illness and its associated stressors (e.g., hospitalisations, missed school and social opportunities, and pain), young people living with PAH face specific unique additional difficulties around ART adherence and well-being, stemming from multiple caretaking transitions and loss due to parental illness or death, loss of siblings, stigma and discrimination, confrontation with mortality and an uncertain future [8].

The current generation of young adults with PAH have often additionally experienced suboptimal ART regimens, many being born in the era of mono- and dual-antiretroviral therapy, thus increasing their likelihood of drug resistance [9]. Rates of viral suppression are variable globally, associated with poor ART adherence [10]. Adherence to ART remains unsatisfactory and varies between 27% and 80% across different populations in various studies [11]. A systematic review of 50 studies from 53 countries reported a pooled level of 62% good adherence (mostly assessed in relation to viral suppression) among youth [10]. There is evidence of higher levels of adherence in some recent studies. For example, of young adults living with PAH who attended a tertiary youth-friendly service in London, UK, 81% had an undetectable viral load (< 200 copies RNA/ml) [12]. Despite improvements in viral suppression rates across specific subpopulations, the lowest rates of viral suppression are among young people aged 13–24 when compared with younger children or older adults [9]. A recent UK cohort study found that adolescents with HIV had poorer outcomes on ART (viral suppression and good immune status) compared with younger children [13]. This trend of poor outcomes has been observed to continue in young adults with perinatal HIV following transition to adult care, and data show lower rates of ART uptake in young adults living with PAH compared with youth with behavioural acquisition [14, 15] highlighting a key population who may need additional support to achieve the same level of treatment success [13].

ART adherence is dependent on retention in care. There are particular challenges in eastern and southern Africa to retaining people living with HIV in care, with a large number lost to follow up after initiating treatment, particularly for young people [16]. In this region, the proportion of all people with HIV who knew their status was 85% in 2018 with an estimated 67% on treatment, and 58% virally suppressed (up from 43% in 2015). There is a shortage of evidence on the most effective approaches for young people living with PAH failing to achieve or sustain viral suppression due to non-adherence [17].

Unprotected sexual intercourse in young people living with HIV in the context of globally variable ART coverage and low rates of viral suppression [18] presents a risk of onward (potentially drug resistant) HIV transmission to partners and to offspring. For many young adults, regardless of their HIV status, negotiating their first sexual experiences can be complex and the importance of condom use may vary depending on cultural and religious norms [19, 20]. For young people with PAH, sexual onset will occur alongside their knowledge of having a sexually transmittable, stigmatised medical condition.

Sharing an HIV-positive status with others has the potential to facilitate positive outcomes in the above areas. It is now accepted that successful viral suppression (< 200 copies HIV RNA/ml) with ART prevents HIV transmission to sexual partners (Undetectable = Untransmittable; U = U) [21, 22]. In situations where viral suppression has not been achieved, however, sharing an HIV-positive status with partners may reduce onward HIV transmission, by fostering communication about safer sex. Indeed, sharing HIV status with partners has been estimated to reduce risks of onward HIV transmission by 18–61% [23, 24]. HIV status sharing may also encourage a partner to undergo testing, use prevention strategies such as condoms, pre-exposure prophylaxis (PrEP) and post-exposure prophylaxis (PEP), and engage in care/treatment if needed [25].

Although young adults who have an undetectable viral load may not have to share their status to prevent onward HIV transmission, sharing has been shown to have a number of personal benefits in addition to its public health benefits [26]. Sharing may help to buffer HIV-related stress and improve well-being [27, 28]. Being open about one’s HIV status may facilitate obtaining social support from significant others such as families and peers, which in turn is a prerequisite for constructive coping, enhanced self-esteem and other health-promoting behaviors [28]. Sharing of one’s HIV status may also enhance ART adherence, due to greater adherence support from partners, friends or family and a reduced need to hide medication use in situations where sharing has not occurred [29, 30]. This is particularly important even for young adults who have an undetectable viral load as they will only remain undetectable if they continue to adhere to ART. Fear of sharing HIV status is commonly cited as a barrier to ART adherence in young people living with PAH [31]. There is also evidence of lower levels of HIV status sharing being associated with poorer engagement with HIV care [32, 33].

Globally, there are low rates of sharing an HIV-positive status with a partner, ranging from 39–97% [34]. This may be even lower in young people with PAH. Birungi, Obare, Mugisha, Evelia and Nyombi [35] reported that only 38% of their sample of youth with PAH in relationships (aged 15–19 years) had shared their HIV status with their current partner. Lee and Oberdorfer [36] found that 48% of their sample of adolescents (aged 13+) living with PAH had never shared their status to anyone. Only 40% of young adults living with PAH in the US reported sharing with all or most of their partners in a recent study, and almost half (45%) reported sharing with no partners when having unprotected sex [25]. In a study in Uganda and Kenya, only one in five participants (adolescents aged 13–17) reported having shared their HIV status with their peers [28].

Sharing an HIV status carries a unique challenge for young people with PAH with concerns about revealing their mother’s (and other family members’) HIV status [37]. Negative parental sharing attitudes, including directives to not share, may be internalised [37] with an atmosphere of secrecy and limits to open communication about HIV affecting the young person at home, in their community and in the clinic [38, 39]. The subjective difficulty of sharing one’s HIV status in young people with PAH, particularly in relationships, has been frequently reported, with a fear of rejection, a lack of confidence about sharing (disclosure self-efficacy), and fear of secondary disclosure from the recipient to others cited as barriers to sharing [37, 40–42].

There remain important risks of sharing ones’ HIV status, including the threat of rejection, humiliation, stigma and even violence [25, 43]. However, overall, there may be more potential benefits of sharing ones’ HIV status. Hence, for other groups of people living with HIV, there have been efforts to develop HIV status-sharing interventions. Conserve et al. [34] reviewed interventions promoting HIV sharing to sexual partners. Three of the five studies included in this review (four of which focused on MSM, the other minority women) showed rates or frequencies of HIV sharing that were greater in the intervention condition than the control condition, with small-to-medium effect sizes reported. Kennedy et al. [44] reviewed interventions promoting HIV status sharing to *any* recipient in low- and middle-income countries. Seven of the nine studies where outcomes were reported showed a significantly greater level of HIV sharing in the intervention compared with the control arm, with small-to-medium effects. There are no HIV status-sharing interventions specifically designed for young people with PAH, or young people with HIV more generally [45]. Facilitating sharing is often a small component of multi-component interventions for youth with HIV, but this component is rarely evaluated [46]. A recent systematic review of interventions to improve retention in HIV care and adherence to ART among youth highlighted the need for further development and testing of multi-faceted interventions, to address broader social barriers to adherence and retention [47].

Consistent with the gaps in the evidence base outlined above, there is a lack of sharing guidance to support young people with PAH or professionals working with this population [45]. The World Health Organisation (WHO) has called for work in this area, specifying the need for interventions to help adolescent disclosure decision-making, support caregivers and train providers (WHO, 2018). There is evidence that young people with HIV [48–50] and health care workers [51] would like more HIV status-sharing support.

Given the gap in the evidence base, and the importance of the issue, we aim to develop and test the feasibility of a behavioural intervention to increase sharing levels and satisfaction with sharing decisions in perinatally infected young adults in the UK and Uganda in a 30-month project. The appropriateness of the intervention in high-income/low-prevalence (e.g., UK) and low-income/high-prevalence (e.g., Uganda) contexts needs to be assessed, given evidence of low rates of sharing in both. The target population will be aged 18–25 years, due to higher rates of sexual activity, with potentially more active consideration of sharing than in younger populations, as well as higher mortality and morbidity in this age group [12]. In addition, in this age range, decisions about sharing may be less constrained by others than during earlier adolescence. The focus will be on sharing with any recipient depending on participant preference. Enhancing sharing with one category of recipient could facilitate sharing with other categories. For example, increased sharing and communication with friends and family has been shown to be associated with sharing with a partner [25, 42].

We hypothesise that (1) the intervention will be feasible, in relation to recruitment, retention and acceptability and (2) participants in the intervention group will have a higher rate of sharing in the previous 6 months at follow-up than participants in a standard-of-care (SOC) group.

## Methods/design

### Study settings

The study will take place in two countries (list of study sites available on request):
UK. Participants will be recruited from five inner city NHS clinics which provide services for young people living with PAH across two cities, as well as from one UK-based HIV charity.Uganda. Participants will be recruited from a not-for-profit organisation in one city, providing HIV care to young people living with PAH ≥ 18 years.

### Phase 1—intervention development and adaptation (12 months)

This phase will involve (1) assessing barriers and facilitators to HIV status sharing, with questions informed by an intervention development framework [52], (2) developing a theory of HIV sharing relevant to the study contexts, (3) developing intervention and recruitment strategies, (4) carrying out formative assessment of intervention components for feasibility, understanding and acceptability, (5) manualising the intervention, (6) developing semi-structured interview guides, (7) developing a fidelity measure for the intervention, (8) developing a measure to describe standard of care, (9) training therapists delivering the intervention, (10) developing methods to assess intervention costs in phase 2 and (11) developing and adapting measures of primary and secondary outcomes and other variables (e.g., ART adherence self-efficacy). The latter task will involve producing linguistically and culturally validated measures where none exist for the Ugandan context, through translating existing questionnaires/items and response options, back translation by a different translator, reviewing of translated items by a local expert panel and cognitive interviewing of ten young people taking part in phase 1 in Uganda.

Individual assessments and focus groups will be used. Participants for this stage will involve the following:
Ten young people with PAH in the UK and ten in Uganda:
*Inclusion criteria:*
Aged 18 to 29 years inclusive in the UK, and 18 to 25 inclusive in Uganda (the wider age range in the UK reflects the greater difficulty in recruiting from the population, given its relatively smaller size compared with Uganda);Living with PAH;Knowledge of own HIV status;Able to give informed consent*Exclusion criteria*:
Current serious mental health problems. Clinician opinion will be sought regarding the assessment of any mental health difficulties that might render young people unsuitable for the study;Moderate-to-severe learning disability/executive functioning difficulties. Individuals with clinically documented moderate-to-severe cognitive difficulties will be excluded;Current serious physical health problems with life expectancy < 12 months, according to clinician opinion;Current participation in other psychosocial intervention/support researchFriends, family and partners of young people with PAH in the UK (ten individuals) and in Uganda (a further ten).
*Inclusion criteria*:
Friends, family or partners of people currently or recently aged 18–29 years living with PAH in the UK, 18–25 years in Uganda;Awareness of the HIV status of the young person with PAH;Five professionals working with young people living with PAH in the UK and five in Uganda
*Inclusion criteria*:
Current or recent involvement in the care of the people aged 18-25 living with PAH.

### Phase 2—main study: feasibility trial

#### Study design

This component of the study uses a multi-site randomised feasibility design. Participants will be randomised to either the intervention or standard of care. Assessments will be carried out at three time points—pre-intervention/baseline (for both conditions), post-intervention (at the end of the final session, only for the intervention condition), and 6-month follow-up (6 months from baseline, both conditions). See Fig. 1 for a flow diagram of the Phase 2 study design.

**Fig. 1 Fig1:**
[figure not shown]
Flow diagram of Phase 2 study design

### Sample

The sample size will be 94 per condition (intervention or standard of care; 188 participants in total: 47 in each condition in each country). This sample size has been chosen to allow for study attrition so that at least 64 participants per condition will be retained in the study.

#### Sample size calculation

The sample size of 32 in each condition in each country has been chosen to both assess primary outcomes, and to be sufficient to enable differences of between 0.5 and 1 standard deviation to be observed between conditions with 80% statistical power across secondary outcomes (e.g., changes in rates of HIV status sharing). Half a standardised difference would require 64 per condition, and one standard deviation difference would require 16 per condition.

#### Inclusion criteria

The following are included in the study:
Aged 18 to 25 years inclusive;Living with PAH;Receiving HIV care at study sites;Knowledge of own HIV status

#### Exclusion criteria

The following are excluded in the study:
Current serious mental health problems. Clinician opinion will be sought regarding the assessment of any mental health difficulties that might render young people unsuitable for the study;Moderate-to-severe learning disability/executive functioning difficulties. Individuals with clinically documented moderate-to-severe cognitive difficulties will be excluded.Current serious physical health problems with life expectancy of < 12 months, according to clinician opinion;Inability to understand or communicate in English (UK) or either English or Luganda (Uganda) according to clinician opinionCurrent participation in other psychosocial intervention/support researchParticipation in phase 1 of this studyParticipation of another individual within the household

### Intervention condition

The intervention condition will consist of four sessions (90 min per session) delivered in a mixed group/individual format (three group sessions including seven or eight participants/one individual session); professionally led (therapist one); mixed gender; face-to-face; with peer mentor involvement (therapist two) and follow-up support. These features were preferred by clinic attendees in survey of 57 young people with PAH in the UK [53] and were seen as feasible in a second survey of 16 professionals working with this population in the UK [54].

The intervention will aim to develop motivation and skills for HIV status sharing, increase HIV status sharing self-efficacy, decrease anxiety about HIV sharing and increase satisfaction with HIV status sharing decision-making. Motivational interviewing (MI) and Cognitive behavioural therapy (CBT) will guide the intervention. The intervention will be delivered by two therapists in each country. One will be a health professional (not a mental health specialist). The other will be a peer worker.

The content of the intervention is based on models of HIV disclosure decision-making and HIV disclosure anxiety [55–58] and existing evidence of HIV status-sharing correlates, barriers and facilitators [25, 28, 59]. In particular, disclosure attitudes, normative beliefs, self-efficacy, planning and support are argued to be important proximal determinants of HIV status sharing. These factors are suggested to be influenced by more distal factors: personal values and HIV stigma.

The content of specific sessions will be as follows:
Session 1—Engaging: ground rules, living with HIV, previous experiences of HIV sharing (and evaluation of these experiences), defining HIV status sharing (as a process), understanding HIV status-sharing anxiety, risks and benefits of disclosure and non-disclosure in specific situations and with different recipients, and values clarification exerciseSession 2—Focusing and evoking: HIV sharing wants and needs, eliciting and reinforcement of personal HIV-sharing decision rules, exploring discrepancy between decision rules/current HIV status sharing and values, and examining evidence for HIV status-sharing anxietySession 3—Developing HIV status-sharing skills: identifying barriers and facilitators to HIV status sharing, responding to others’ reactions to HIV status sharing, HIV sharing strategies; developing HIV-sharing decision (if…then) rules, HIV status-sharing communication skills, use of social support (identifying safe/special people to disclose to), managing HIV status-sharing anxiety (challenging anxious thinking), HIV-sharing hierarchies including level of HIV sharing and level of anxiety about response, setting HIV-sharing goals, and planning to disclose (how, where and when)Session 4—Individual goal setting and planning: personal feedback from assessment; assessing HIV-sharing readiness; goal setting; who, how and when to disclose (action planning, using HIV-sharing decision aid); coping with HIV-sharing consequences over time (coping planning); using pre and post HIV-sharing support for self-disclosure recipient; safer sex skills (including condom use); considering nature of relationship with potential recipient, level of HIV sharing, and method of HIV sharing; ways to minimise risk of adverse outcomes/overcome barriers/respond to adverse responses; accepting possibility of adverse outcomes; and producing a personalised HIV-sharing plan

We will use role play, modelling, cognitive restructuring and behavioural exposure techniques, with both video material and group discussions integrated with interactive exercises. We will aim to space out the sessions to allow reflection on HIV sharing or actual sharing to take place between sessions. Follow-up emotional, informational and problem-solving support (in the 6 months from baseline to the follow-up data point) from a peer worker will be provided for both young people exposed to the intervention and people whom they have disclosed to. This will involve the use of both phone and online/social media options [60].

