***Enrolment, randomisation (both conditions) and baseline assessments (standard-of-care condition only)***

The study coordinator will arrange the enrolment visit at the end of the consent process if the study coordinator has taken consent. If the clinician has taken consent, the study coordinator will contact the participant to arrange the enrolment visit. If the study coordinator and the participant are able to carry out the enrolment process at the same time as consent is obtained, this will be offered. At the enrolment visit, the participant will be enrolled into the study and given a study ID. Personal information will be recorded by the study coordinator in the participant’s personal study register (name, contact details, etc.) and non-identifiable information will be recorded in the central study register (study ID, date of enrolment, etc.).

Stratified block random allocation to condition by country/site (UK inner city NHS clinics and Uganda) will be used. There will be 12 blocks of either 15 or 16 participants per block (six blocks in Uganda, five blocks in London and one block in Birmingham). Computer-generated randomisation will be used using the Research Randomizer. The randomisation will be carried out by the study PI in the UK and the site PI in Uganda. Allocation will be concealed from the study coordinator in each country through the use of sequentially numbered opaque envelopes. The study coordinator will inform the participant which condition that they have been allocated to.

If the participant is in the standard-of-care condition, the baseline assessment will then be administered by the study coordinator, who will also record clinical information from the clinical notes or database for participants in this condition. Travel expenses will be paid to participants in both the intervention and the standard-of-care conditions if any have been incurred and a receipt will be kept.

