The effect of the intervention on secondary outcomes will be carried out separately for each country. Two tailed tests will be used. Exploration via multivariate analysis will also be carried out if there is sufficient data to support this approach. Sufficient data refers both to missing data (although we will impute data if this is minimal, e.g., <5%) and to the number of observations (e.g., if attrition results in a lack of statistical power to investigate multivariate relationships).

Independent *t* tests (where parametric assumptions were met) and chi-squared tests will be used to compare baseline characteristics of those retained in the study to those lost to follow up to examine whether there are any systematic differences between these groups. We will interpret our findings on secondary outcomes in light of this ‘lost to follow up’ analysis. We will aim to obtain follow-up data from all participants enrolled in the study regardless of the extent of involvement in intervention activities.

The extent to which participants in the intervention condition naturally use HIV disclosure ‘change talk’ (language indicating preparation for and commitment to disclosing their HIV status) in the final individual session will be calculated using the Motivational Interviewing Skills Code (MISC) 2.5 coding manual [88]. The relationship between the frequency of disclosure change talk and any HIV status sharing at the 6-month data point will be calculated using logistic regression analysis.

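### The sample size calculation makes no allowance for group delivery in the intervention arm, so the stated 80% power at 0.5 SD is overstated if outcomes correlate within groups

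*Protocol article*

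**What the plan says.** All from the protocol article.

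- **Intervention condition:** four sessions, of which three are shared: "three group sessions including seven or eight participants/one individual session". One pair of therapists delivers them in each country.
- **Standard-of-care condition:** usual clinic care, with no structured sessions on sharing and so no treatment groups.
- **Sample:** "188 participants in total: 47 in each condition in each country", planned so that at least 64 per condition are retained.
- **Sample size calculation:** "The sample size of 32 in each condition in each country" is meant to allow "differences of between 0.5 and 1 standard deviation to be observed between conditions with 80% statistical power across secondary outcomes". The supporting figures are "Half a standardised difference would require 64 per condition, and one standard deviation difference would require 16 per condition". No ICC, design effect or grouping is mentioned.
- **Enrolment and randomisation:** "There will be 12 blocks of either 15 or 16 participants per block", six of them in Uganda and six in the UK.
- **Data management and analysis, Phase 2 main study:** effects on secondary outcomes are examined by country, with a pooled exploration described as preliminary. "Two tailed tests will be used", but no between-arm test or model is named. The independent t and chi-squared tests are assigned to comparing retained with lost participants. Within the intervention arm, a logistic regression relates change talk to any sharing at 6 months, with no group term mentioned.

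**The concern.** This is a partially nested design: one arm is treated in groups and the other is not. Members of a group share discussion, role play and modelling, and the article names normative beliefs among the proximal determinants of sharing. Some within-group correlation in the outcomes is therefore plausible. It inflates the variance of the intervention-arm mean, so a sample size derived for independent participants gives less power than it claims.

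Higher sharing in the intervention arm is the article's second hypothesis, and limited efficacy is one of the criteria for moving to a full trial. A definitive trial of the same intervention would also need an ICC for its own sample size, and this study can supply a first estimate only if group membership is recorded.

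**Working it through.** **1. Reproduce the plan's figure.** Inputs: differences of 0.5 and 1 SD, 80% power and two-sided tests, as stated. Alpha is not stated; 0.05 is assumed. For independent participants, n per condition = 2(1.960 + 0.842)²/d².

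- d = 0.5: 62.8, so 63; the exact noncentral t gives 64 (power 80.1%).
- d = 1: 15.7, so 16; the exact t gives 17.
- One-sided tests would give 50 and 13, which do not match.

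So 64 and 16 are independent-observations figures.

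**2. Number and size of groups (inferred).** Half of a block of 15 or 16 is 7 or 8, the stated group size, and 47/6 = 7.8. That suggests about six groups per country, 12 in all. At 32 retained per condition per country, each group keeps 32/6 = 5.33 members. As a less favourable case, take m = 7.5, where groups stay full and losses fall on whole groups (64/7.5, about 8.5 groups).

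**3. Allow for grouping in the intervention arm only.**

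- Design effect in that arm: DE = 1 + (m − 1) × ICC
- SE of the difference, in SD units: √((DE + 1)/64)
- Power at 0.5 SD: Φ(0.5/SE − 1.960)
- Difference detectable with 80% power: 2.802 × SE
- Retained n per condition for 80% power: 64 × (DE + 1)/2
- Type I error of a test that ignored groups: 2[1 − Φ(1.960 × SE₀/SE)], with SE₀ = √(2/64) = 0.177

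Example, m = 5.33 and ICC 0.05: DE = 1 + 4.33 × 0.05 = 1.217; SE = √(2.217/64) = 0.186; 0.5/SE = 2.687; power = Φ(0.727) = 76.6%.

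| m | ICC (assumed) | DE | Power at 0.5 SD | Detectable difference | n for 80% | Type I if groups ignored |
|---|---|---|---|---|---|---|
| – | 0 | 1.000 | 80.7% | 0.50 | 64 | 5.0% |
| 5.33 | 0.02 | 1.087 | 79.1% | 0.51 | 67 | 5.5% |
| 5.33 | 0.05 | 1.217 | 76.6% | 0.52 | 71 | 6.3% |
| 5.33 | 0.10 | 1.433 | 72.7% | 0.55 | 78 | 7.6% |
| 7.5 | 0.02 | 1.130 | 78.2% | 0.51 | 69 | 5.7% |
| 7.5 | 0.05 | 1.325 | 74.6% | 0.53 | 75 | 6.9% |
| 7.5 | 0.10 | 1.650 | 69.0% | 0.57 | 85 | 8.9% |

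These use the normal approximation. With Satterthwaite degrees of freedom, (v₁ + v₂)²/[v₁²/(k − 1) + v₂²/(n − 1)], where v₁ = DE/64, v₂ = 1/64, k = 12 and n = 64, power at m = 5.33 is 74.1% at ICC 0.05 (32.7 df) and 69.8% at ICC 0.10 (29.2 df).

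**4. By country (32 per condition).** The detectable difference is about 0.70 SD under independence (0.71 by exact t). With SE = √((DE + 1)/32), ICC 0.02–0.10 raises it to 0.72–0.77 SD (m = 5.33) or 0.72–0.81 SD (m = 7.5). Power at 1 SD with Satterthwaite degrees of freedom and ICC 0.10 is 92% (m = 5.33) or 86% (m = 7.5). At 0.5 SD it is about 50% even under independence, so the figure of 64 applies only to the pooled comparison.

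**The case against.** **The analysis is not shown to ignore groups.** A reader might infer that the planned tests treat participants as independent and will give standard errors that are too small. The article does not support that. It names no between-arm test, its t and chi-squared tests serve the attrition comparison, and an analysis plan not shown may include a group term. This objection stands: the type I error column describes what would happen if groups were ignored, not what is planned. The only outcome model named is the change-talk regression, and there too silence is not proof.

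**The claim is a range, and most of it survives.** The article claims power for differences between 0.5 and 1 SD. By country, the detectable difference stays inside that range at every ICC used here. This also stands, but the article gives 64 as the requirement at 0.5 SD, and that endpoint has no margin.

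**The size rests on an assumed ICC.** At 0.02 the loss is one to three percentage points. Hence the conclusion is conditional.

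**The groups are inferred.** Nothing says that one block forms one group or that membership is fixed. Participants state timetable preferences and may miss a session and continue. The range for m covers part of this uncertainty.

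**Little depends on it.** The primary outcomes are recruitment, retention and acceptability, reported descriptively, and the sample is separately justified by the precision of the retention rate. That limits the consequence but does not make the power figure right.

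**Conclusion.** The point holds for the power statement. The figure of 64 per condition assumes independent participants although one arm is treated largely in groups, so 80% power at 0.5 SD is overstated if the ICC is above 0. For ICC 0.02 to 0.10, pooled power is about 79% to 73% with 5.3 retained per group, or 78% to 69% with 7.5. This rests on an assumed ICC, an assumed two-sided alpha of 0.05, and about 12 groups inferred from the randomisation blocks. Reading it as proof of invalid tests goes beyond the document. The shortfall is negligible at the low end and moderate at the high end, and concerns secondary outcomes only. The correction is worth making because it is cheap and corrects a stated figure.

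**What to change.** 1. Under Sample size calculation, restate the power at 0.5 SD over an assumed ICC range (for example 0.02 to 0.10), or restate the detectable difference as about 0.51–0.57 SD. No extra enrolment is needed for a feasibility trial.
2. Record an intervention group identifier for each participant, with the group actually attended at each session.
3. State that secondary-outcome models, by country as the article already plans and in the pooled exploration, include a random group effect in the intervention arm only, with small-sample degrees of freedom. The by-country analysis need not be replaced by a pooled one.
4. Allow for group in the change-talk logistic regression.
5. Report the ICC with its interval for use in planning a full trial.

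The cost is one extra variable and some wording. Intervals become slightly wider, and about six groups per country leave few degrees of freedom. The ICC will be imprecise: with 12 groups of about five, its approximate standard error is 0.09–0.11, about as large as or larger than the values assumed here. It should be reported as a planning range rather than a point estimate.
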